### Participants and recruitment

2.3

The recruitment posters will be displayed in the hospitals and community. And the forward recruitment information will be posted on WeChat to recruit the potential participants for this study. The participants will be explained in detail about the potential benefits and services to be provided and the risks associated with participating in the study, including the possible associated adverse clinical outcomes with viscera massage therapy. An informed consent will be signed after reading carefully by each participant prior to the participation. On the consent form, participants will also be asked whether they agree to use their data even if they opt out of the trial. The participants will also be required to obtain permission for the research team to share relevant information with staff from the participating hospitals or regulatory agencies. The participants will receive 4 different courses of viscera massage therapy. The personal information of all the participants will be kept confidential by the researchers and used only for this study. The patients must properly understand and sign informed consent. The FBG and 2hPG will be used to potentially determine whether participants meet the inclusion criteria. Patients who met the criteria will be included in the study (Fig. 1).

**Figure 1 F1:**
[figure not shown]
Trial flow chart.

### Diagnostic criteria

2.5

The diagnostic criteria refer to “Intervention for adults with prediabetes: A Chinese expert consensus.”^[20]^ The participants will have to meet the following criteria: the blood level of IFG should be at 6.1 mmol/L < FPG < 7.0 mmol/L and 2hPG < 7.8 mmol/L, the blood level of IGT should be at FPG < 7.0 mmol/L while 2hPG ≥7.8 mmol/L, but <11.1 mmol/L, and the IFG+IGT should meet the two states above meanwhile.

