#### Blood sample

2.11.2

Blood samples will be taken from each participant twice—one before the first treatment, and the other following the last treatment. Measurements will include triglycerides, total cholesterol, low-density lipoprotein cholesterol, and high-density lipoprotein cholesterol, FBG, 2hPG, and HbA1c, fasting insulin and HOMA-IR.

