#### Statistical method

2.11.5

SPSS23.0 statistical software will be used for statistical analysis for all the data generated. Chi-square test will be used for enumeration data. Paired *t* test will be used for the comparison of measurement data before and after the treatment. One-way analysis of variance (ANOVA) will be used for comparison between the groups, with *P* < .05 as difference and *P* < .01 as significant difference.

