## Discussion

3

Prediabetes is defined as blood glucose levels above normal but below diabetes thresholds, with hyperglycemia and insulin resistance the major threads.^[7]^ Prediabetes includes IFG, IGT, and IFG+IGT. The IFG subjects always have high hepatic insulin resistance with almost normal values in skeletal muscle, while high insulin resistance in skeletal muscle with only modest changes in liver insulin sensitivity is commonly in IGT subjects.^[3]^ The incidence of prediabetes is rising as the prevalence of obesity increases globally.^[7]^ So, in this trial, we will select not only the common indicators of prediabetes, such as FBG, 2hPBG, and HbA1c, but also the indicators associated with obesity, like weight, BMI, WC, WHR, WHtR, and blood lipid level. And studies have found that a combination of WC and WHtR may be a better clinical utility than BMI and WHR in identifying individuals with cardiometabolic risk factors.^[21]^ Fasting insulin and HOMA-IR will be used to test the level of insulin resistance. Through the proposed clinical trial, the effect of AM on prediabetes and obesity will be further verified.

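### FBG and 2hPG are compared between arms with no entry-state or baseline term, although the entry rules mix states with different starting levels and define the mixed state impossibly

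*Protocol article*

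**What the plan says.** Protocol article, section 2.5 (Diagnostic criteria) admits three states. For IFG, "the blood level of IFG should be at 6.1 mmol/L < FPG < 7.0 mmol/L and 2hPG < 7.8 mmol/L". For IGT, "the blood level of IGT should be at FPG < 7.0 mmol/L while 2hPG ≥7.8 mmol/L, but <11.1 mmol/L". For the mixed state, "the IFG+IGT should meet the two states above meanwhile". Section 2.3 makes these two markers the screening test: "The FBG and 2hPG will be used to potentially determine whether participants meet the inclusion criteria".

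Section 2.11.2 (Blood sample) measures "FBG, 2hPG, and HbA1c, fasting insulin and HOMA-IR", plus lipids, in every participant before the first and after the last treatment.

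Section 2.11.5 (Statistical method) plans a paired t test within groups and a one-way ANOVA between groups. It adds that "Chi-square test will be used for enumeration data". It names no entry-state factor and no baseline covariate. Section 2.2 (Setting) allocates 40 per group by odd or even serial number in order of enrolment and does not stratify.

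The Discussion treats the states as physiologically distinct: "The IFG subjects always have high hepatic insulin resistance with almost normal values in skeletal muscle", with the reverse pattern described for IGT.

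**The concern.** The entry rules build known differences in starting level into the sample. Every IFG entrant is below the 2hPG limit and every IGT entrant is at or above it. FPG must be raised in IFG but need not be in IGT. When two arms of 40 are compared by a one-way ANOVA without a term for this, the spread between states goes into the error variance, and any chance difference in the mix goes into the estimated arm difference.

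At stake is the precision and readability of the FBG and 2hPG comparisons, the two markers by which the trial defines prediabetes. The information needed to remove the problem is already collected at screening and before treatment.

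**Working it through.** **1. The entry rules side by side (section 2.5, mmol/L)**

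| State | FPG | 2hPG |
|---|---|---|
| IFG | above 6.1, below 7.0 | below 7.8 |
| IGT | below 7.0, no lower limit | at least 7.8, below 11.1 |
| IFG+IGT | both rules at once | below 7.8 and at least 7.8: impossible |

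Three things follow.
- Only one pairing is normal by definition: IFG entrants on 2hPG. IGT entrants may have FPG of 6.1 or less, or between 6.1 and 7.0.
- HbA1c, fasting insulin and HOMA-IR have no entry limit.
- The mixed class is empty as written, and the people it presumably describes (FPG between 6.1 and 7.0 with 2hPG of at least 7.8) already fall under the IGT rule. Who may enter is still clear, but entry state cannot be recorded in three levels.

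**2. Chance imbalance in the mix**

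Inputs: n = 40 per arm (section 2.2); p = share of entrants in one state (not given, so assumed); entry state taken as unrelated to serial number.

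SE of the difference in shares = √(2·p(1−p)/n); 95% range = ±1.96 × SE.

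- p = 0.5: √(2 × 0.25/40) = 0.112, so ±22 percentage points.
- p = 0.3: √(2 × 0.21/40) = 0.102, so ±20 points.
- p = 0.2: √(2 × 0.16/40) = 0.089, so ±18 points.

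**3. What this does to 2hPG**

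Let g be the difference in mean 2hPG between states that is still present at follow-up (not given, so assumed). The shift in the arm difference is imbalance × g. At p = 0.5:

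- g = 1 mmol/L: ±0.22 × 1 = ±0.22 mmol/L.
- g = 2 mmol/L: ±0.22 × 2 = ±0.44 mmol/L.

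The same effect seen as variance is p(1−p)g² = 0.25 × 1² = 0.25 or 0.25 × 2² = 1.00 (mmol/L)². These are two views of one quantity and must not be added: √(2 × 1.00/40) × 1.96 = 0.44. The ANOVA standard error already contains this variance, so the result is lost precision, not a false test.

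The calculation applies if follow-up values are compared. Section 2.11.5 does not say whether follow-up values or changes are analysed. With changes, much of a stable gap would cancel.

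For FBG the same formula applies, but section 2.5 does not fix the sign or size of a gap, because IGT entrants may lie in the IFG range.

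**4. The plan's own sample size**

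Section 2.2 gives 36 and recruits 40 per group, but names no outcome, effect size, SD or power. The figure cannot be reproduced, so the shifts above cannot be set against a planned effect.

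**The case against.** The strongest case on the other side has four parts.

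- **Pooling matches the objective.** Section 2.1 asks about prediabetes as a whole, and the pooled comparison estimates the average effect in that population without bias from pooling. This stands.
- **Covariates and subgroups are often left to an analysis plan that is not shown.** This stands for subgroup reports and supportive analyses. It carries less weight for the between-arm method, which section 2.11.5 does state: a one-way ANOVA has no place for a second factor or a covariate.
- **The supporting text does not show that response differs by state.** The Discussion concerns the site of insulin resistance. The Introduction reports a more significant decrease in postprandial than in fasting glucose, which may refer to size or to P value, and it says both fell. This stands. The point rests on different starting levels, not on a proven difference in response.
- **The chi-square test may be meant for baseline counts such as sex.** This stands, so naming the test is not a defect.

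Two stronger readings are tempting. A reader might infer that the effect is diluted by a known factor. If a share f cannot respond, the required sample grows by 1/(1−f)², which is 1.56, 2.04 or 4.0 for f = 0.2, 0.3 or 0.5. This needs an assumed mix and exactly zero response below a cut-off. The document gives neither, and values below 7.8 can still fall.

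A reader might also infer that no outcome shows whether prediabetes improved. That is not so: FBG and 2hPG define the state and are measured again after treatment. Only a combined, categorical version is not named.

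**Conclusion.** The point holds in a limited form. Section 2.5 makes 2hPG at entry differ by state by rule and lets FPG differ, while the stated analysis and allocation take no account of state or baseline. The cost is precision and exposure to chance imbalance in the FBG and 2hPG comparisons, not bias in the average effect.

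The size is about ±22 percentage points in the mix at 40 per arm under an assumed 50:50 split (±18 at 20:80). That corresponds to ±0.22 to ±0.44 mmol/L in the 2hPG arm difference if the states stay 1 to 2 mmol/L apart, also an assumption, and if follow-up values are compared. Any weakening of the effect through smaller response in entrants normal on a marker is plausible but cannot be calculated from the document.

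The contradiction in the mixed-state definition needs no assumption and must be resolved before entry state can be used.

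**What to change.** 1. Reconcile the definitions in section 2.5 so that each eligible person falls into exactly one state. The mixed state cannot require 2hPG both below 7.8 and at least 7.8, and the overlap of the IGT rule with FPG between 6.1 and 7.0 must be settled. Which limits apply is for the investigators to decide.
2. Record entry state for each participant from the screening FBG and 2hPG.
3. In section 2.11.5, replace the one-way ANOVA for FBG and 2hPG with a between-arm model of the follow-up value that includes entry state, the baseline value of that marker, or both. Fix the choice before the data are seen.
4. Optionally, as a secondary and supportive outcome only, prespecify the proportion who at week 4 no longer meet the reconciled entry limits, compared by the planned chi-square test. Values that have risen past the upper limits should not count as improvement. This count is less sensitive than the means and should not replace them.

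The cost is a slightly more complex model and few participants per entry state, so results within a state would be imprecise. No new measurement or visit is needed. Balancing allocation on entry state is a further option but is not essential once the model adjusts for it.

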### Inclusion criteria

2.6

The participants will have to meet the diagnostic criteria of prediabetes in the Expert Consensus on Intervention of Adult Prediabetes in China, and fulfill the following conditions: they will have to meet the diagnostic criteria for obesity or overweight. They must be above the age of 18. Their Score of the American Diabetes Association Diabetes Risk Self-Test Questionnaire must be ≥25 points. They must have no other acute or chronic diseases. They must be failure in diet and exercise efforts in the early stage. They must voluntarily accept massage treatment. They must have the ability to use smart phones and social media platforms. They will have to sign the informed consent and accept the lifestyle intervention pushed by the WeChat public platform.

### Exclusion criteria

2.7

However, the subjects will not be able to participate in this trial, if they meet any of the below indicated criteria: Patients who have been diagnosed with diabetes or other endocrine diseases, such as thyroid disease being treated. Patients who have been diagnosed with acute cardio-cerebrovascular events or myocardial infarction within 6 months. Patients who have severe impairment of liver and kidney function (Alanine transaminase, Aspartate Aminotransferase >2 times the upper limit of normal value, abnormal serum creatinine). The patient was in ketosis or hyperosmolar state. The patient was unable to exercise or required to have a special diet due to physical illness. Patients who was withdrawal, refusal of treatment, and unwillingness to exercise diet intervention during treatment. Patients who have uncontrolled hypertension (systolic blood pressure ≥160 mm Hg, diastolic blood pressure ≥110 mm Hg). Patients who have participated in similar studies or plan to undergo surgery to lose weight. Patients who are pregnant.

### Termination of the standard

2.8

After enrollment, the trial will be effectively terminated if one of the following symptoms occurs: the patients suffer from the severe side reactions that may occur during the course of the study (medical certificate issued by the observing doctor), and severe complications or deterioration of the subjects during the study period. The subjects request to willingly withdraw from the clinical study halfway. Patients who may be uncooperative and have poor compliance. In addition, if the conditions for the termination of the test must be met after being processed by the competent doctor in accordance with the standardized working procedure, the test will be terminated immediately. The researchers will keep a detailed record of the reasons and time of withdrawal of the participants from the study. Patients with the untreated time exceedingly at least 1/2 course of treatment will be able to enter the efficacy statistics and must properly maintain a random medical record number.

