**Methods and design::**

Eighty prediabetes individuals will be recruited for this study. Eighty prediabetes individuals will be divided into lifestyle intervention group and viscera massage + lifestyle intervention group by a simple random method. Each group will have 40 individuals. The manipulation of the viscera massage + lifestyle intervention group will be mainly carried out through rubbing the abdomen, kneading abdomen, vibrating abdomen, and pressing the abdomen, 30 minutes per time, once a day, with 2 days off every 5 days. Lifestyle interventions will be performed by combining pushing healthy lifestyle guidance information through Wechat application and giving face-to-face advice together daily. The lifestyle intervention group will receive healthy lifestyle intervention only. All the intervention will be conducted for 4 weeks. Weight, body mass index (BMI), waist circumference, waist-to-hip ratio, and waist-to-height ratio will be measured at the last day of every week. Triglycerides, total cholesterol, low-density lipoprotein cholesterol, high-density lipoprotein cholesterol, fasting blood-glucose, 2-hour post-meal blood glucose (2hPG) and glycosylated hemoglobin, fasting insulin and insulin resistance index will be tested at the first day and last day of the intervention course. The fecal samples of subjects will be gathered at the first day and last day of the intervention course and will be performed 16S rRNA gene sequencing and metagenomic detection. Finally, the effect and potential mechanism of viscera massage on prediabetes will be discussed in combination with all the results.

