### Stripping and shedding criteria

2.9

After enrollment, patients who meet one of the following criteria will be terminated from the trial. The stripping criteria: those who might fail to meet the inclusion criteria and have entered the study. Those who might to follow the prescribed treatment or incomplete data affecting the efficacy evaluation and safety evaluation. Those who might have used the different therapeutic methods prohibited by this protocol. Those who might change the treatment plan midway by themselves. The shedding criteria: the subjects with poor compliance and self-withdrawal during the course of treatment. Those who might display serious adverse events or in those in which complications might occur. Those who will be unable to continue the treatment for various reasons.

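### The only sentence on which withdrawn patients enter the efficacy statistics sets a minimum of untreated time, apparently reversed, and measures it in a course that the protocol uses in two ways

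*Protocol article*

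**What the plan says.** Section 2.8 (Termination of the standard) lists grounds for stopping, requires the reason and time of each withdrawal to be recorded, and then states: "Patients with the untreated time exceedingly at least 1/2 course of treatment will be able to enter the efficacy statistics". No other sentence in the article says who enters the efficacy statistics.

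Section 2.9 (Stripping and shedding criteria) opens by saying that "patients who meet one of the following criteria will be terminated from the trial". Its shedding list includes "the subjects with poor compliance and self-withdrawal during the course of treatment" and "Those who will be unable to continue the treatment for various reasons". Its stripping list includes "incomplete data affecting the efficacy evaluation and safety evaluation".

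The word *course* appears in two senses and is not formally defined:

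- Abstract, Methods and design: the laboratory measures "will be tested at the first day and last day of the intervention course", which implies a single course with one first and one last day.
- Section 2.3: "The participants will receive 4 different courses of viscera massage therapy".

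Section 2.10 gives the schedule for all patients: daily treatment, two days off after every five, for 4 weeks. Section 2.3 also says that the consent form asks about use of data after a participant opts out.

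**The concern.** A rule that lets withdrawn patients into an efficacy analysis normally requires that they received enough treatment. This one requires that they went without it for long enough. It may be a translation slip, but the printed text is the rule, and the two readings favour nearly opposite groups of withdrawals: early stoppers on the literal wording, late stoppers on the presumed intention.

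Correcting the direction alone would not be enough. With *treated* in place of *untreated*, entry would still depend on how long a person stayed on treatment after allocation. If persistence differs between massage plus lifestyle and lifestyle alone, for reasons related to outcome, the between-group comparison in section 2.11.5 is no longer between the groups as allocated. Section 5 acknowledges the lack of double-blind control, so knowledge of the assigned treatment can influence both persistence and how an unclear rule is applied.

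**Working it through.** No stated sample size, power or significance level bears on this point. The check is a reading of the text plus simple session counts.

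**Inputs.** Five sessions in each 7-day cycle and a duration of 4 weeks (section 2.10); one course (Abstract) or four (section 2.3). That the four courses are equal and one week each is an assumption; section 2.3 does not say so.

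**Schedule.** 4 weeks × 5 sessions = 20 sessions, over 4 × 7 = 28 days.

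**Half-course threshold** = (20 ÷ number of courses) ÷ 2.

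- One course: 20 ÷ 1 ÷ 2 = 10 sessions, or 28 ÷ 2 = 14 days (50% of the regimen).
- Four equal courses: 20 ÷ 4 ÷ 2 = 2.5 sessions, or 28 ÷ 4 ÷ 2 = 3.5 days (12.5% of the regimen).

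Under that assumption the thresholds differ by 10 ÷ 2.5 = 4 times.

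**Two illustrative withdrawals.** One stops after 15 sessions (20 − 15 = 5 missed), the other after 5 (20 − 5 = 15 missed). The table shows whether each meets the entry condition.

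| Reading | Stops after 15 | Stops after 5 |
|---|---|---|
| Untreated (as printed), threshold 10 | no (5 < 10) | yes (15 > 10) |
| Untreated (as printed), threshold 2.5 | yes (5 > 2.5) | yes (15 > 2.5) |
| Treated (presumed intention), threshold 10 | yes (15 > 10) | no (5 < 10) |
| Treated (presumed intention), threshold 2.5 | yes (15 > 2.5) | yes (5 > 2.5) |

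With a single course, reversing the direction swaps the two patients. With four weekly courses, both qualify in either direction.

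**Sections 2.8 and 2.9 side by side.** Section 2.9 says who leaves the trial; section 2.8 says who enters the statistics. A person can leave and still be analysed, so the shedding list and the entry rule can coexist. The stripping clause is harder to fit. It acts on patients whose incomplete data affect the efficacy evaluation, and section 2.11.2 places the second blood sample after the last treatment. A patient who stops early may therefore lack a complete end-of-treatment record. That patient would be stripped under section 2.9 and admitted under section 2.8, and the article does not say which rule prevails.

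**The case against.** The strongest reply is that the sentence is permissive. It says that certain patients may enter and does not say that others may not. Read that way, it means that even those who missed half a course can be analysed, which is close to analysing everyone allocated. It is true that no *only* is printed, so the document does not establish that late stoppers are excluded; the table shows who meets the stated condition and no more. But a threshold that grants entry implies that something differs below it, and the sentence does not say *even*. If the permissive meaning was intended, the same rewording would express it.

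A second reply is that a condensed article leaves analysis sets to a fuller document. That would answer a complaint about an omission. Here a rule is stated, and stated wrongly.

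A reader might also infer several stronger points that the documents do not support:

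- *That section 2.9 contradicts section 2.8.* It governs termination, and section 2.3 foresees use of data after opting out.
- *That the rule cannot be applied to the lifestyle arm.* Section 2.10 puts all patients on the same daily schedule, with daily face-to-face advice, so that arm has days to count.
- *That the threshold is known to vary fourfold.* This needs four equal weekly courses. The phrase in section 2.3 could be loose wording for the four massage techniques.
- *That set membership will be decided after the data are seen.* Nothing says so.
- *That keeping under-treated patients is itself the error.* An analysis of everyone allocated keeps them too.

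**Conclusion.** The point stands in limited form. The entry rule in section 2.8 is worded as a minimum of untreated time, apparently the reverse of what was meant. In either direction it ties the efficacy set to compliance after allocation, in a trial without double-blind control. The threshold is uncertain: 10 of 20 sessions if the course is the whole 4 weeks, or 2.5 if four equal weekly courses are assumed. The stripping clause on incomplete data is unreconciled with it.

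The number of patients affected cannot be given, because no dropout rate is stated. For scale, section 2.9's neighbouring rules aside, section 2.2 recruits 40 per group and regards more than 36 per group as sufficient. Leaving four people out of one group gives 40 − 4 = 36, which no longer exceeds that figure. The conclusion about direction and dependence on compliance rests on the printed wording alone; only the 2.5-session figure needs the added assumption.

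**What to change.** 1. Remove the sentence in section 2.8 as a gate. State that the main efficacy analysis includes everyone allocated, in the group allocated, using available outcome data also from those who stop early and consent to its use.
2. If a compliance-based set is wanted, make it secondary. Define it as a stated minimum of treatment received out of the 20 scheduled days, with the same rule in both arms.
3. Use *course* in one sense throughout, and reconcile the Abstract with sections 2.3, 2.8 and 2.9. Say in particular how the incomplete-data clause relates to the main analysis.

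The cost is slight rewording and a possibly diluted effect estimate. As an illustration only, assume that 36 per group was set for 80% power at two-sided 5%, which the article does not state; by normal approximation this implies a standardised difference of 0.66. With 40 per group analysed, power is 0.84 without dilution. It is 0.80 if 10% of the massage arm gain half the effect, 0.71 if 30% gain half, and 0.54 if 30% gain none. Excluding these patients would not recover that power without cost, since it reduces the numbers and gives up the comparison of the groups as allocated.
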